## Methodology

### Study design

This is a randomized, double-blinded, placebo-controlled trial via telemedicine. Eligible subjects will receive a maximum of 14 days’ treatment with Yinqiao Powder-Maxing Ganshi Decoction (with or without specified additions) or placebo, and will be followed up on days 7, 14 and 35 after receiving medication (day 0).

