### Inclusion criteria

1. Age from 18 to 65 years;2. Tested positive for COVID-19 by RATs, Deep Throat Saliva (DTS) or Throat/Nasal swab RT-PCR tests;3. Patient diagnosed with mild to moderate COVID-19 based on the “Coronavirus disease 2019 (COVID-19) Treatment Guidelines” published by National Institutes of Health, United States;4. Duration of symptoms ≤72 h (Start from the presence of the major symptoms of COVID-19: Fever: oral temperature >37.2°C, or cough score ≥2, or fatigue score ≥2);5. At the moment of screening (or within 2 h before screening), body temperature: >37.2°C6. Diagnosed with pattern of wind and heat invading the exterior (風熱犯表證) and/or pattern of intense exuberance of lung heat (肺熱熾盛證) by a registered Chinese medicine practitioner (CMP) (Diagnostic criteria are the corresponding criteria in the “Diagnosis standards for common syndromes in traditional Chinese medicine (《中醫常見證診斷標準》)” published by “Diagnostic Subcommittee of China Association of Traditional Chinese Medicine (中華中醫藥學會中醫診斷學分會)” in 2008, with ≥20 as the threshold for determination);7. Explicit declaration of willingness to participate in the study at the time of video-conference screening after reading the electronic informed consent form (written consent form will have to be signed after inclusion).

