
Subjects in the treatment group will receive CM granules in dosages equivalent to the decocting piece dosages shown above according to the IMP manufacturer’s illustration (estimated granule weight per dose: 33.4–59.7 g), and will be dissolved in hot water and administered while it is warm. Participants will take 1 dose a day, and the medication will be divided into two portions, with one in the morning and the other in the evening after meal. The time of treatment and medication is 14 days at maximum or until patients get negative RAT results on two successive days and the major symptoms subside (define as oral temperature ≤37.2°C, the score of cough and fatigue ≤1). The actual duration is determined by the patient according to their own condition, and they can also seek advice from the research team or registered CMPs though the direct phone line if necessary.

The CM granules are planned to be a mixture of single granules produced by PuraPharm, a commercial company in Hong Kong. Most of these granules are made from botanical drugs used in CM, with some made from fungi (*Lasiosphaera Calvatia, Poria*), animal (*Margaritifera Concha*), and mineral (*Gypsum Fibrosum*). They are turned into granules by using modern methods that mimic the old way of making CM decoction. PuraPharm is the main provider of these granules to Hong Kong’s hospitals and health institutions. The botanical, animal and mineral drugs meet the standards of Chinese Pharmacopoeia if they are included. This company follows the GMP standards of the PRC, Australia and the US for quality control and production. It also has an ISO 17025 certified laboratory to check the quality.

The placebo was made from Sorbitol, Maltodextrin, Corn Starch, Soluble Fiber, Black Bean Extract, Abelmoschus esculentus Extract, Green Tea Extract, Caramel Color Powder, Citric Acid and Ginseng Flavo, whose appearance, smell and taste was similar to the CM granules. Subjects will be instructed to take them in the same way as in the treatment group. Each study subject will be given relevant information on the use and storage of IMPs. The granules of both treatment and placebo group will be produced by a manufacturer with a GMP certificate.

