#### Baseline randomization (day −1 or 0)

Eligible subjects will be assessed by our registered CMPs via telemedicine in this trial, during which medical history and concomitant medication will be recorded. After stratification, subjects will be randomly assigned in a 1:1 ratio to receive up to 14 days of either modified Yinqiao Powder-Maxing Ganshi Decoction (about 33.4–59.7 g each day) or placebo granules (about 33.4–59.7 g each day). Specifically, the stratified randomisation is based on age (A: “18–49 years old” and B: “50–65 years old”) and the number of vaccination (a: “received 3 or more doses - fulfilling government vaccination requirement” and b: “received 2 doses or less of vaccine - yet to be fully vaccinated”). Subjects will be divided into two groups by age: one group is “18–49 years old” and the other one is “50–65 years old”; then they will be further divided into two groups within the different age group by the numbers of vaccination: one group is “received 3 or more doses of vaccine, and the another is “received 2 doses or less of vaccine”. Four subgroups will be created after stratification and subjects in each subgroup will be randomly assigned to either the treatment or placebo group. The distribution of age and number of vaccinations between the two groups will be roughly comparable after stratified randomisation. The IMP will be prescribed by Registered CMPs and will be sent to patients by delivery service. The current Western medicine treatment can continue during the study period.

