#### Follow-up assessment (Days 7, 14) and end-of-study assessment (Day 35)

Subjects will have video consultation on day 7 (±1 day) and day 14 (±1 day) and post treatment follow up at day 35 (±1 day) (Table 1). Subjects are required to measure their body temperature and oxygen saturation twice daily; conduct RATs, clinical symptom score measurement and tongue image capture once daily during the day 0–14 (or until the body temperature returns to normal for 24 h/the day the RAT is negative for 24 consecutive hours, whichever is later). Subjects also need to score their symptoms and capture their own tongue image at day 35. All subjects are required to keep a daily record on their body temperature, oxygen saturation, result of RATs, symptom scores, IMP compliance and adverse events. A direct telephone line will be provided so that subjects can report any adverse event during office hours. The subjects will be recommended to attend Emergency Department at the nearest hospital beyond office hours if deemed necessary. In order to ensure compliance, supermarket shopping vouchers worth 300 Hong Kong dollars will be provided to all subjects by registered mail upon completion of the study. Compliance with medication will be assessed by asking subjects about their remaining medication on the remote assessment (days 7, 14 and 35) and by patient diaries completed by the subjects which will be sent back to the research team after the day 35 assessment.

**TABLE 1 T1:** Study schedule.

Items	Screening	Treatment period			End of study visit
	−1 to 0 days	Day 0	Day 7 (±1 days)	Day 14 (±1 days)	Day 35 (±1 days)
Explicit consent on virtual screening	X				
Eligibility	X				
Medical consultation and assessment	X		X	X	X
Medical history	X				
Concomitant medication	X		X	X	X
AE/SAE assessment			X	X	X
Prescription and dispensing of IMP	X				
Medication		X (Max: 14 days)			
Body temperature and oxygen saturation measurement, RAT and tongue image taken		X (14 days or until recovery)			X
Subjects’ daily record for study		X			

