### Study outcomes

#### Assessment

1. The time between starting medication and body temperature returning to normal and the recurrence rate of fever after momentary recovery. Each subject will be issued with the same type of oral thermometer for measurement at 9 a.m. (±2 h) and 9 p.m. (±2 h) daily, with at least 12 h between each measurement. Normal oral temperature is defined as equal to or below 37.2°C. Temperature recovery time is defined as the total number of days between medication starting date and the date of “normal oral temperature for 24 h without antipyretic” (both days inclusive). Subjects are required to measure the temperature until day 14 or on the day when the temperature has remained normal for 24 h, whichever is later.2. The negative rate of RATs at day 14 and negative conversion time. Each subject will be issued with the same type of RAT kits which can be used for at least 14 days for testing at 9 a.m. (±2 h) each day, with at least 24 h between each test. Negative conversion time is defined as the total number of days between the medication starting date and the date of securing two successive negative RAT results (both days inclusive). Subjects were required to undergo testing until day 14 or the day when two successive negative RAT results at least 24 h apart are obtained, whichever is later.3. The remission rate at day 14 and remission time of major symptoms.4. The disappearance rates at day 14 and disappearance time of symptoms. Subjects are required to record the status of their symptoms including major clinical symptoms daily at 9 p.m. (±2 h). Except for fever which is marked as ‘No’ or ‘Yes’ according to whether the oral temperature exceeds 37.2°C, other symptoms will be graded on a scale of 0–4 from “None”, “Mild”, “Moderate”, “Severe” and “Very Severe” depending on the actual feelings of the subject (“None” means the symptom is not present, “Mild” means the symptom is present but does not interfere with daily activities; “Moderate” means the symptom is present and slightly interferes with daily activities; “Severe” means the symptom is present and most daily activities cannot be done; “Very Severe” means the symptom is present and interferes with all daily activities). Major clinical symptoms include fever, cough and fatigue. Remission is defined as oral temperature ≤37.2°C, cough and fatigue score ≤1; disappearance is defined as the symptom being present at day 0 (score >0) but the symptom score is 0 at the date of recording.5. All-cause mortality at the 21st day after stopping the medication.6. Incidence of the progression to severe or critical illness during the trial. The all-cause mortality at the 21st day after stopping the medication and the incidence of the progression to severe or critical illness during the trial will be confirmed by communication with the subjects and/or other related person(s) or checking their medical record in the Hospital Authority. The definitions of severe and critical illness are based on the related definitions of “Coronavirus disease 2019 (COVID-19) Treatment Guidelines” published by National Institutes of Health (severe illness: oxygen saturation in the indoor environment of sea level <94%, oxygenation index [PaO2/FiO2] < 300 mmHg, respiratory frequency >30 breaths/min, lung infiltrates >50%; critical illness: respiratory failure, septic shock, and/or multiorgan dysfunction or failure).7. Utilization rates of antipyretic, Paxlovid and molnupiravir within 14 days and the total dosage(s) of the drug(s) used. In this study, subjects are allowed to take western medicines prescribed for the treatment of COVID-19 under the current guidelines of the Hong Kong Hospital Authority with at least 2 h’ gap between Chinese and western medicines. If oral temperature >39.0°C and continues over 4 h; or the oral temperature >39.5°C, the patient is advised to take antipyretic (paracetamol is recommended as a priority) for acute treatment. Patients need to record the amount and time of the drug(s) used.8. Oxygen saturation. For safety reasons, each subject will be issued with the same type of pulse oximeter for measurement at 9 a.m. (±2 h) and 9 p.m. (±2 h) daily, or whenever the subject decides it is necessary. If the reading is less than 94%, the patient is considered to have severe illness and has reached the end point of the study and is recommended to seek medical attention immediately. Subjects are required to measure their oxygen saturation at rest until day 14 or the time of body temperature returning to normal (continuing for 24 h) or the negative conversion time (2 successive negative RAT results), whichever is later.

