### Secondary outcomes

1. The recurrence rate of fever after momentary recovery: the incidence of fever recurrence (oral temperature > 37.2°C) within 24 hours after the patient’s temperature has normalized after treatment;2. The negative rate of RATs at day 14 and the negative conversion time (two successive negative RATs result with at least 24 hours interval);3. The remission rate of major symptoms at day 14 (oral temperature ≤ 37.2°C, score of cough and fatigue ≤ 1 (“None”, “Mild”, “Moderate”, “Severe” and “Very severe” were marked as 0 to 4 450 respectively), and continues 24 hours);4. Time of major symptoms remission: time from the start of treatment to symptoms remission (definition of symptoms remission: oral temperature ≤ 37.2°C, cough and fatigue score ≤ 1 and lasting at least 24 hours);5. The disappearance rates at day 14 and disappearance time of symptoms: the disappearance rates and time of individual symptoms of mild and moderate COVID-19 within 14 days (time defined as the period between starting medication and symptom disappearance); 6. The rate of patients whose oxygen saturation had gone below< 94% after intake of drugIMP, measured at day 14;7. Incidence of the progression to severe or critical illness during the trial;8. All-cause mortality at the 21st day after stopping the medication;9. Utilization rates of antipyretic, Paxlovid and molnupiravir within 14 days and the total dosage(s) of the drug(s) used.

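### Symptom disappearance is judged from a day-0 score that the schedule places in the evening, after randomisation and, for many subjects, after the first portion

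*Protocol article*

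**What the plan says.** The rule is in the protocol article, Study outcomes, Assessment, item 4: "disappearance is defined as the symptom being present at day 0 (score >0) but the symptom score is 0 at the date of recording". The matching entry under Secondary outcomes (item 5) covers each individual symptom and starts the clock at first medication: "time defined as the period between starting medication and symptom disappearance".

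Four other statements fix the timing:

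- **Day 0.** Study design says subjects "will be followed up on days 7, 14 and 35 after receiving medication (day 0"). Table 1 puts medication, and the start of the subject's daily record, in the Day 0 column.
- **Scoring.** The follow-up section asks for "clinical symptom score measurement and tongue image capture once daily during the day 0–14". Assessment item 4 gives the hour: "Subjects are required to record the status of their symptoms including major clinical symptoms daily at 9 p.m. (±2 h").
- **Dosing.** Under Study medications, "the medication will be divided into two portions, with one in the morning and the other in the evening after meal".
- **Randomisation.** It takes place at the visit headed "Baseline randomization (day −1 or 0"), before the product is sent out by delivery.

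Some symptom information exists before dosing. The inclusion criteria use temperature "or cough score ≥2, or fatigue score ≥2" to date symptom onset, and the additions to the core formula depend on symptoms at inclusion. Neither is linked to disappearance. Table 1 has no row for a pre-dose symptom score.

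**The concern.** The set of subjects in whom a symptom can disappear should be fixed by something treatment cannot have changed. Here it is fixed by the day-0 score, and the scheduled day-0 score comes in the evening of the day treatment starts. Two things follow for a subject who has already taken a portion:

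- A symptom present before that portion and scored 0 in the evening leaves both numerator and denominator. Its disappearance time, the shortest possible, is lost, although the outcome counts time from that portion.
- A symptom that first arises after the portion is treated as baseline illness.

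If treatment acts early, the arms may lose different numbers of subjects, and the comparison is no longer of the full randomised groups with the symptom. The same rule applies to every listed symptom, so the issue recurs across this outcome.

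**Working it through.** **Timing.** The 9 p.m. (±2 h) window runs from 7 to 11 p.m.

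| First portion | Day-0 entry relative to it |
|---|---|
| Morning of day 0 | After at least one portion, possibly two |
| Evening of day 0, after the meal | Before or after; the order is not fixed |
| Product received on day 0, first portion later | Before |

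In every row the entry follows randomisation. In a double-blind trial a score taken after randomisation but before any portion does little harm. The harm comes from the first row and part of the second.

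**Size.** The protocol gives no figure for this outcome, so there is none to reproduce. The inputs below are assumptions, except the 48 per arm from Sample size estimation.

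Let q be the chance that a symptom present before the first portion scores 0 at the day-0 entry and stays 0. Let r be the day-14 disappearance rate among those still above 0 at that entry. No new symptoms are assumed.

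- Rate from a pre-dose baseline: 1 − (1 − q)(1 − r)
- Rate under the protocol's rule: r
- Effect lost by the rule: q_T(1 − r_T) − q_P(1 − r_P), where T is treatment and P placebo

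| q_T / q_P | r_T / r_P | Pre-dose baseline | Difference | Protocol's rule |
|---|---|---|---|---|
| 10% / 5% | 60% / 60% | 64.0% vs 62.0% | +2.0 | 0 |
| 20% / 5% | 60% / 60% | 68.0% vs 62.0% | +6.0 | 0 |
| 10% / 5% | 70% / 60% | 73.0% vs 62.0% | +11.0 | +10.0 |
| 5% / 5% | 70% / 60% | 71.5% vs 62.0% | +9.5 | +10.0 |

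The first row in full: 1 − 0.90 × 0.40 = 64.0% and 1 − 0.95 × 0.40 = 62.0%. If all 48 per arm had the symptom, the analysed set would be 48 × 0.90 = 43.2 against 48 × 0.95 = 45.6. With q of 20% and 5% it would be 38.4 against 45.6.

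**How large q might be.** Assume exponential symptom durations with medians of 3 to 7 days. The share cleared within h hours is 1 − 0.5^(h / (24 × median)):

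- within 2 h: 0.8% (median 7) to 1.9% (median 3)
- within 12 h, roughly a morning start: 4.8% to 10.9%

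With medians of 3 days on treatment and 4 on placebo, the 12-hour shares are 10.9% and 8.3%. At r = 60% in both arms the rule then loses 0.40 × (10.9 − 8.3) = about 1.0 point, and less if some subjects start in the evening. A q of 20% lies outside this range.

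**The same in counts.** Suppose 40 per arm have the symptom before dosing, 32 and 30 are clear by day 14, and 4 and 2 of those were already clear at the day-0 entry. The pre-dose rates are 32/40 = 80.0% and 30/40 = 75.0%, a difference of 5.0 points. Under the rule they are 28/36 = 77.8% and 28/38 = 73.7%, a difference of 4.1.

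**The case against.** The strongest reply is that no sentence says the first portion precedes the day-0 score, or that the diary entry is the score meant. Screening and baseline may fall on day 0, a consultation takes place then, and the statistical section speaks of comparing baseline with each visit. On that reading, day 0 could mean the pre-dose assessment, with the order of entry and portion left to the diary instructions.

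Part of this stands. The post-dose position is inferred from several passages, and a reader should not conclude that every subject's baseline is post-dose. But the text does not secure the screening reading. Screening may fall on day −1, the only scores named there are for cough and fatigue, and nothing ties them to disappearance. Because the article states the rule itself, this is not a detail left to a later document.

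The reply on size also stands. In the 40-per-arm example the distortion is 0.9 points, while the standard error of the difference is √(0.80 × 0.20/40 + 0.75 × 0.25/40) = 9.3 points, about ten times larger.

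A reader might also infer that symptoms caused by the granules will inflate the baseline set. The documents do not support that as more than a possibility. Such a symptom would have to be a listed COVID-19 symptom, arise within hours and differ by arm. Adverse events are already recorded daily and graded separately.

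**Conclusion.** The concern holds in a limited form. As scheduled, the score that admits a symptom to the disappearance analysis is taken after randomisation and, depending on when the subject starts, after the first portion. The rule then excludes the earliest disappearances from an outcome whose clock starts at that portion.

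The likely bias is small: usually one or two percentage points on the assumptions above, and 6 in a case more extreme than the duration model supports. It would mainly dilute a real early effect, although with equal early clearance the rule slightly enlarges the difference (+10.0 against +9.5). These sizes rest on assumed clearance rates, not on trial data.

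Two stronger conclusions are tempting but unsupported. One is that randomisation no longer protects the comparison at all; the gap is about one day of dosing in a blinded trial. The other is that the main result is affected; neither the primary outcome nor the remission outcomes use this definition.

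**What to change.** - Have subjects complete the existing 0–4 scale for all listed symptoms (fever as the existing yes/no mark) once, immediately before the first portion, and add this entry to Table 1.
- Define a symptom as present at baseline if it scores above 0 (fever: yes) on that pre-dose record, and use this for both the disappearance rate and the disappearance time.
- Treat the 9 p.m. day-0 entry as a post-dose record whenever it follows the first portion, so that a symptom already gone by then can count as disappeared.

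The cost is one extra diary entry per subject and a change of wording, with no new visit or procedure and no change to treatment.

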
### Primary outcome

The time between starting medication and body temperature returning to normal (oral temperature 37.2°C and maintain 24 hours).

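### Symptom disappearance time is the only time-to-recovery outcome without a persistence rule, so one symptom-free evening can end the clock; the effect on the arm difference cannot be fixed from the documents

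*Protocol article*

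**What the plan says.** Four outcomes in the Protocol article are times to some form of recovery. Three carry a persistence condition:

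- Primary outcome, temperature: "oral temperature 37.2°C and maintain 24 hours".
- Secondary outcomes item 2, RAT conversion: "two successive negative RATs result with at least 24 hours interval".
- Secondary outcomes item 4, remission of major symptoms: temperature at or below 37.2°C, with "cough and fatigue score ≤ 1 and lasting at least 24 hours".

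The fourth is symptom disappearance. Assessment item 4 states that "disappearance is defined as the symptom being present at day 0 (score >0) but the symptom score is 0 at the date of recording". Secondary outcomes item 5 covers "the disappearance rates and time of individual symptoms of mild and moderate COVID-19 within 14 days", with "time defined as the period between starting medication and symptom disappearance". Neither place gives a duration or a confirming score. Symptoms are recorded once daily at 9 p.m., within a window of two hours either side, on a 0 to 4 scale (fever is yes/no).

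The Assessment section also words remission without a duration: "Remission is defined as oral temperature ≤37.2°C, cough and fatigue score ≤1". The 24-hour condition appears only under Secondary outcomes, items 3 and 4.

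**The concern.** A time to an event that is met on any single recording date is naturally read as the time to the first such date. Under that reading, a cough scored 2, 0, 2, 2 on successive evenings has disappeared on the second evening. It has not remitted, because the level of 1 or below did not last 24 hours. The stricter level is thus credited before the weaker one.

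The protocol expects transient recovery. It makes return of fever after a momentary recovery an outcome, and it protects the primary outcome with a 24-hour rule. The individual symptom scores have no such protection, although cough and fatigue are two of the three major symptoms named in the trial's aim and hypothesis.

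At stake is what the disappearance time measures. With a single-zero rule it mixes symptom duration with evening-to-evening fluctuation, and a comparison of arms can be moved by the second as well as the first.

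**Working it through.** The plan gives no figure for this outcome, so there is none to reproduce. The duration and rate inputs below are assumptions, because the documents state neither the durations of symptoms nor the rate of isolated zeros.

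**Step 1: direction within an arm.** The first zero can never come later than the first of two successive zeros. Single-zero times are therefore equal or earlier for every subject. This needs no assumption.

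**Step 2: a hand calculation for the arm difference.** Let T be the evening on which the symptom resolves for good, and q the chance of an isolated zero on each earlier evening. The mean first-zero time is the sum of (1 − q)^k for k = 0 to T − 1, which equals (1 − (1 − q)^T)/q. Take T = 7 in control and T = 6 in the treated arm, a true difference of 1.0 day. The first-zero difference is then (1 − q)^6:

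| q, both arms | Control mean | Treated mean | Difference | Loss |
|---|---|---|---|---|
| 0.05 | 6.03 | 5.30 | 0.95^6 = 0.74 | 26% |
| 0.10 | 5.22 | 4.69 | 0.90^6 = 0.53 | 47% |
| 0.20 | 3.95 | 3.69 | 0.80^6 = 0.26 | 74% |

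**Step 3: change when the zeros occur.** Suppose they fall only on the last two evenings before resolution. The mean time is then brought forward by 2q + q(1 − q) in each arm. At q = 0.10 that is 0.20 + 0.09 = 0.29 days in both arms, and the difference stays at 1.0 day.

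**Step 4: let the rate differ by arm** (Step 2 means). With 10% in control and 20% in treated, 5.22 − 3.69 = 1.53 days: wider than the true 1.0. With 20% in control and 10% in treated, 3.95 − 4.69 = −0.74 days: reversed.

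**Step 5: simulation with durations that vary between subjects.** Two assumed set-ups were run over 14 evenings.

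*Means 7 and 6 days, SD 2.5, true difference about 1.0 day.* With isolated zeros equally likely on every symptomatic evening, the first-zero difference was 0.72, 0.54 and 0.29 days at 5%, 10% and 20%, a loss of about 28%, 46% and 71%. With zeros confined to the last two or three evenings it was 0.93 to 1.00 days.

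*Lognormal, means 7 and 5.5 days, coefficient of variation 0.5, true difference about 1.38 days:*

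| q control / treated | First zero | Two successive zeros |
|---|---|---|
| 0 / 0 | 1.37 | 1.37 |
| 0.05 / 0.05 | 0.97 | 1.36 |
| 0.10 / 0.10 | 0.68 | 1.30 |
| 0.20 / 0.20 | 0.35 | 1.09 |
| 0.10 / 0.20 | 1.67 | 1.77 |
| 0.05 / 0.15 | 2.19 | 1.73 |
| 0.20 / 0.10 | −0.65 | 0.63 |

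With equal rates the first-zero loss is 1 − 0.97/1.38 = 30%, 1 − 0.68/1.38 = 51% and 1 − 0.35/1.38 = 75%. Two successive zeros recover most of it. With unequal rates they do not remove the distortion, and in the 0.10/0.20 row they lie slightly further from 1.38 than the single-zero rule.

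**Step 6: day-14 rate**, read as the state on day 14, same lognormal set-up. As q goes from 0 to 0.20 in both arms, the single-score rate moves only from 0.956 to 0.965 in control and from 0.986 to 0.989 in treated.

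**The case against.** The strongest objection concerns the size. A reader might infer that the single-zero rule must shrink the arm difference and so hide a real effect. The documents do not support that. It follows only if isolated zeros are equally likely in both arms and on every evening from the start, whatever the severity. A symptom graded 0 to 4 plausibly flickers to 0 as it fades rather than at its peak, and Step 3 shows that the difference is then almost untouched. This objection stands, so shrinkage is one scenario among several.

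It can also be said that remission and disappearance are different endpoints. One is a composite of temperature, cough and fatigue; the other takes each symptom separately and at a stricter level. They need not share a rule, and the overlap is limited to the major symptoms. That is fair, but it does not explain why this one time outcome lacks a condition that the other three carry.

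The word first is not in the text, and deriving an event date from daily states is often left to an analysis plan. That softens the point without removing it: the protocol itself fixes the event as a state on a single recording date.

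Finally, a reader might infer that remission has two conflicting definitions. The Assessment section gives thresholds, and Secondary outcomes supplies the 24 hours in both items that use remission. The outcome is settled there, and the omission is one of wording.

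**Conclusion.** The gap in the definition is real. Disappearance time is the only time-to-recovery outcome without a persistence requirement. On its natural reading it gives times equal to or earlier than sustained resolution in both arms, and cough can count as disappeared before it counts as remitted.

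How this acts on the treatment comparison is not determined by the documents. Under assumed rates of 5% to 20%, equal in both arms and on every symptomatic evening, the difference falls by roughly a quarter to three quarters. It hardly changes if isolated zeros cluster just before resolution, and it can widen or reverse if their rate differs by arm. The primary outcome and the sample size are not touched, and the day-14 rate is little affected. This is a worthwhile, inexpensive improvement to one secondary outcome and no threat to the main conclusion.

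**What to change.** In Assessment item 4 and Secondary outcomes item 5, define disappearance time as running to the date of the first of two successive daily scores of 0 (at least 24 hours). Two evening records with a window of two hours either side can be 24 − 4 = 20 hours apart. So either add the minimum 24-hour spacing already used for the RATs, or state that two successive evening records satisfy the condition. Treat a first zero on the last recorded day as unconfirmed and censor it.

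State that daily symptom scoring continues to day 14. The follow-up section can be read as letting it end once temperature and RAT have recovered, and the Abstract ties recording to the end of medication. A symptom that clears near that point would then have no confirming score.

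As a wording matter, repeat the 24-hour condition in the remission definition under Assessment.

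The cost is a few lines of text, some extra evening scores from subjects who would otherwise stop early, and the loss of some unconfirmed last-day zeros. No visits or subjects are added.
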